### Data analysis plan

We will develop a trial database to maintain data from baseline and follow-up questionnaires. Data analyses will be conducted using STATA software. The comparison of smoking abstinence rates (and any other binary outcomes) between the two trial arms will be carried out using OR (and 95% confidence intervals) as the outcome statistic.

The primary outcome will be prolonged abstinence from months four to 12 with no more than five lapses, confirmed by CO < 10 ppm at the 12-month assessment. Participants who decline biochemical verification or who do not respond to follow up will be counted as smokers but those who have died or genuinely moved away will be disregarded from the numerator and denominator. If we detect differences in missing data we will assess the robustness of our primary analyses by using imputation methods such as pattern-mixture models [35].

Exploratory subgroup analyses, including logistic regression analyses with interaction terms, will be conducted to investigate possible effect-modifying variables, including age, gender, socio-economic status, level of nicotine dependence, number of prior quit attempts, and use of pharmacological interventions. These exploratory analyses have low statistical power and are also likely to yield false positive findings so the results will need to be interpreted with great caution.

The analysis of mediating variables will examine hypothesized mechanisms of the intervention. The intervention using the Forever Free booklets teaches skills based on the cognitive-behavioral approach. The effectiveness of coping skills training for relapse prevention depends on (1) the adequate delivery and receipt of the booklets, (2) the acquisition of coping skills by quitters and (3) the application of such skills in high-risk situations. This intervention mechanism suggests certain important process variables that should be investigated in the trial. At the follow-up interviews, we will at first ask trial participants whether they have received the booklets, whether they have read the booklets (and how much time spent and how many booklets they looked at). We will then investigate whether the use of booklets helped in the acquisition of coping skills by the participants, in terms of improved capability to identify risky situations and to know more appropriate ways of handling urges to smoke again. Thirdly, we will ask the trial participants whether they have actually applied the skills learned from the booklets. Finally, we will invite the trial participants to give an overall assessment of the usefulness of the booklets. We will summarize data collected in tables and plots to examine associations between smoking abstinence and important mediating variables (for example, level of the use of booklets, actual application of coping skills in high-risk situations).

We will also use more complex methods for the exploratory mediation analysis according to MacKinnon and Fairchild [36]. As an example, the Single-Mediator model consists of three equations:

(1)Y=i1+cX+e1;

(2)Y=i2+c'X+bM+e2;

(3)M=i3+aX+e3;

where Y is the dependent variable (smoking relapse), X is the independent variable (the intervention), and M is the mediating variable (for example, time spent on reading the booklets, acquisition of coping skills, and so on). Then, the mediating effect of M could be quantified by a*b (or c'-c). These exploratory mediation analyses will help understand how and why the intervention works or does not work.

Using data on time to the first event of smoking relapse, survival curves of the intervention and control arm will be compared by using Cox regression analysis as secondary analyses. This might reveal patterns indicating that relapse is postponed, which could suggest that ‘top up interventions’ might be helpful.

Using data from the trial, we will calculate the mean incremental cost for those in the intervention arm (Forever Free booklets) compared to the control arm. Similarly, the incremental effect of the intervention will be equivalent to the difference in the 12-month quit rate between the two arms. If dominance does not occur (that is, if one intervention is more costly and more effective) [37], the incremental cost and incremental effect will be used to calculate the cost required to have one more long-term quitter with the provision of the Forever Free booklets. The cost-effectiveness analysis will be based on individual level costs and outcome data, with uncertainty expressed as cost effectiveness acceptability curves and if appropriate, CIs for the incremental cost effectiveness ratio. As part of a cost-utility analysis, the incremental QALY gain associated with the intervention will be estimated, based on EQ-5D data collected in the trial and findings from existing studies of relevant economic evaluations [38-40].

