### Sample size

The abstinence rate of four-week quitters at 12 months is estimated to be 25.0% in the control and 32.4% in the intervention group (based on an OR of 1.44). Assuming alpha = 0.05 and 1-beta = 0.8 and a dropout rate of 15%, about 1,400 patients will be required in total (700 in each arm) [31]. To simplify the project management, we will recruit participants mainly from the core Stop Smoking clinics in Norfolk.

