### Baseline and follow up data collection

At the four-week session following the quit date, stop smoking advisors will gather baseline information from participants who have consented to be in the trial. The information collected includes participants’ demographic characteristics (for example, age, gender, and occupation), heaviness of smoking index, smoking and quitting history, and level of confidence to remain abstinent.

The consensus statement of the Society for Research on Nicotine and Tobacco (SRNT) and the Russell Standard both suggest that prolonged abstinence should be the primary outcome of a smoking cessation trial [32,33]. The normal form of prolonged abstinence allows a two week grace period in which lapses do not invalidate abstinence following quit day to assess the outcome of aid to cessation trials. However, a relapse prevention intervention might reasonably prevent lapses (occasional smoking) from becoming relapses (fulltime smoking and abandonment of the quit). Therefore, we propose a two-month grace period during which lapses to smoking do not count against achieving abstinence. As participants will be four weeks abstinent on enrollment, this equates to the primary outcome being prolonged abstinence from three months after quit day to 12 months follow up. Following the Russell Standard, the primary outcome will be prolonged abstinence from months four to 12 with no more than five lapses, confirmed by CO < 10 ppm at the 12-month assessment. The secondary outcomes will be seven-day self-report point prevalence abstinence at three months and seven-day biochemically confirmed point prevalence abstinence at 12 months.

To assess cost-effectiveness, costs will be estimated from a health service perspective. We will collect data on the resource use associated with self-help materials (including intellectual property, adaptation, printing and postage), any additional stop smoking services and cessation products at follow-up interviews. Our hypothesis is that the intervention, if effective, will improve abstinence rates, reduce repeated use of stop smoking services and might reduce use of other health care. Other resources which might be affected by the intervention will also be monitored, including GP visits and hospital admissions. The EQ-5D [34] will be used to estimate the benefits in terms of the QALY gain associated with each intervention during the study period.

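### The stated primary comparison is an odds ratio between arms with no covariates; pre-specified adjustment for baseline variables already collected would be a valid, nearly free gain in efficiency

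*Protocol article*

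**What the plan says.** Under Data analysis plan, the comparison of abstinence rates, and of any other binary outcome, "between the two trial arms will be carried out using OR (and 95% confidence intervals) as the outcome statistic". No model or covariate is named for it. Baseline factors enter one paragraph later, for a different purpose: "Exploratory subgroup analyses, including logistic regression analyses with interaction terms, will be conducted to investigate possible effect-modifying variables". The factors listed there include age, nicotine dependence, socio-economic status and the number of earlier quit attempts.

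Under Baseline and follow up data collection, advisors record demographic characteristics and "heaviness of smoking index, smoking and quitting history, and level of confidence to remain abstinent" at the four-week visit. According to Participant recruitment and randomization, the baseline questionnaire goes to the coordinator, who then allocates the participant. These values are therefore fixed before allocation. That section describes a computerised allocation system and mentions no stratification factor.

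Under Sample size, abstinence is "estimated to be 25.0% in the control and 32.4% in the intervention group", "based on an OR of 1.44", which leads to 1,400 participants, 700 per arm.

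**The concern.** Heaviness of smoking, quitting history and confidence are plausible predictors of who stays abstinent. The plan considers several baseline factors worth testing as effect modifiers but gives them no role in estimating the main effect. As the article reads, neither the described allocation nor the primary comparison makes use of them.

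Efficiency and pre-specification are at stake; validity is not. With rates of 25.0% and 32.4%, the planned power at the dropout-reduced size is only just above 80%. Information that is already on the database could raise it at no cost in participants. In an open trial there is also some value in fixing the covariate list before results are seen, so that whether and how to adjust is not a later choice.

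**Working it through.** **Inputs from the article (Sample size).** Control rate 25.0%, intervention rate 32.4%, OR 1.44, alpha 0.05 (taken as two-sided, since sidedness is not stated), power 80%, dropout 15%, 700 per arm.

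**Input that the article does not give.** The prognostic strength of the baseline variables. It is assumed below and shown as a range.

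**1. Reproducing the sample size without covariates.**
- OR check: odds 1.44 × 0.25/0.75 = 0.48, so the rate is 0.48/1.48 = 32.4%.
- Formula: n = [1.96√(2p̄(1−p̄)) + 0.842√(p₁(1−p₁) + p₂(1−p₂))]² / (p₂−p₁)², with p̄ = 0.287.
- Numbers: [1.96 × 0.6397 + 0.842 × 0.6376]² / 0.074² = 3.206/0.005476, or 586 per arm.
- Dropout: 586/0.85 = 690 per arm, 1,380 in total. With the unrounded 32.43% the result is 581 per arm and 1,368 in total.

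Both totals are within 3% of 1,400. A plain comparison of two proportions is therefore a sufficient basis for the stated size.

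**2. Power of the unadjusted comparison.** Power = Φ{[(p₂−p₁)√n − 1.96√(2p̄(1−p̄))] / √(p₁(1−p₁) + p₂(1−p₂))}.
- n = 595 (700 × 0.85): (1.805 − 1.254)/0.638 = 0.864, power 80.6%.
- n = 700: (1.958 − 1.254)/0.638 = 1.104, power 86.5%. This applies if the stated rates already count non-responders as smokers.
- n = 700 with the 15% dropouts counted as smokers on top of the stated rates: 0.85 × 25.0% = 21.3% and 0.85 × 32.4% = 27.5%, power about 78%.

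**3. Gain from adjustment, by simulation.** The model was logit P(abstinent) = a + b·arm + s·x, with x one standard-normal baseline score. The marginal rates were held at 25% and 32.4%. Wald tests with and without x were compared over 2,500 trials per setting.

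| Assumed AUC of x | Conditional OR | Power at 595 per arm, unadjusted → adjusted | Power at 700 per arm, unadjusted → adjusted |
|---|---|---|---|
| 0.58 | 1.45 | 81% → 82% | 86% → 86% |
| 0.63 | 1.46 | 81% → 82% | 87% → 88% |
| 0.69 | 1.50 | 81% → 85% | 86% → 89% |
| 0.74 | 1.54 | 81% → 87% | 86% → 91% |
| 0.82 | 1.65 | 81% → 91% | 87% → 95% |

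Runs of 3,000 trials per setting at 595 per arm agree: 81%, 83% and 85% adjusted at AUC 0.61, 0.66 and 0.70, against 80–81% unadjusted, and no loss at AUC 0.5. The Monte Carlo standard error of one power figure is √(0.8 × 0.2/3,000) = 0.7 points, so a 1-point difference is barely distinguishable from none.

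**4. Where the gain comes from.** On the log-odds scale, adjustment does not shrink the standard error. Power rises because the conditional OR lies further from 1 than the marginal 1.44. A true gain in precision appears on the marginal scale. There the risk difference is standardised over the sample: mean of expit(a + b + s·xᵢ) minus mean of expit(a + s·xᵢ). For slopes s of 0.4 to 0.8 (AUC about 0.6 to 0.7) its variance falls by about 4 to 10%. In participants, 1,400/0.96 = 1,458 and 1,400/0.90 = 1,556, so this is worth roughly 58 to 156 extra people.

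**The case against.** The strongest reply is that the plan fixes an outcome statistic and says neither adjusted nor unadjusted. An adjusted logistic model also yields an odds ratio, the choice of covariates is commonly left to the SAP or full protocol, and neither is available here. This stands in part: the SAP may already settle the matter, so the recommendation is conditional. It does not remove the point. The article gives baseline regression an explicit and purely exploratory role, and its sample size follows from a plain two-proportion formula. A two-arm odds ratio is the natural reading.

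Several stronger readings are tempting, and the document does not support them:
- *The unadjusted analysis is invalid or biased.* It is neither. Randomisation justifies it, and the confidence interval already allows for chance imbalance.
- *The baseline variables are strong predictors.* The article lists them and gives no prognostic strength for any. Plausible is as far as one can go, and the size of the gain depends entirely on that assumption.
- *Power is about 80% at best.* That figure removes the dropouts. The Data analysis plan says "Participants who decline biochemical verification or who do not respond to follow up will be counted as smokers", which keeps them in the denominator. If the stated rates already reflect that rule, power at 700 per arm is about 86 to 87%.
- *Adjustment narrows the interval for the log odds ratio.* It does not (step 4).
- *The economic analysis needs a modelled risk difference.* Crude rates already give a difference in quit rates. A standardised one would only be consistent with the adjusted primary analysis.

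**Conclusion.** The point holds as an optional efficiency improvement. No stated figure is wrong, and the planned comparison is valid and coherent with the sample size.

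At 595 per arm, adjustment would add roughly 1 to 5 points of power and reduce the variance of the standardised risk difference by about 4 to 10%. This rests on two assumptions: a combined AUC of about 0.6 to 0.7 for the baseline variables, and the planned 25.0% and 32.4% rates. Below that AUC range the gain fades to nothing, but there is no loss. Gains near 10 points would need an AUC of about 0.82, which nothing in the article suggests.

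**What to change.** Unless the SAP already does so, add to the Data analysis plan that the primary analysis is a logistic regression of prolonged abstinence on arm, adjusted for a short list fixed before outcome data are seen: heaviness of smoking index, confidence to remain abstinent, number of prior quit attempts, and age. Report the standardised (marginal) odds ratio and risk difference with 95% confidence intervals, and the unadjusted odds ratio beside them. Say how a missing covariate value will be handled, so that no one leaves the primary analysis for that reason.

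The cost is a few sentences. These variables are already collected or already named in the plan, so no new data should be needed. State the one downside: the conditional odds ratio is slightly further from 1 (about 1.46 to 1.50 against 1.44 in these scenarios) and is not the quantity used in the sample-size calculation. The marginal estimates keep the result comparable with that calculation.

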The effectiveness of coping skills training differs between population subgroups. Our meta-analysis found that coping skills training for smoking relapse prevention was ineffective for pregnant or postpartum quitters, hospitalized ex-smokers, forced short-term quitters, and smokers with mental health illnesses or drug abusers. For quitters from general communities, coping skills training interventions were not effective for current smokers who were motivated to quit (odds ratio (OR) = 0.96, 95% confidence interval (CI) 0.82 to 1.12) or for those who had quit smoking for less than one week (OR = 1.09, 95% CI 0.88 to 1.36). However, coping skills training interventions significantly reduced smoking relapse in community quitters who, at baseline, had been able to quit for at least one week (OR = 1.44, 95% CI 1.14 to 1.81) [19].

These findings show that the timing of relapse prevention is important and that coping skills training seems effective in secured quitters who are highly motivated to remain abstinent. Clearly, the acquisition of coping skills alone is not sufficient and only those who use these skills really benefit [23]. This evidence can be interpreted in terms of the theoretical mechanisms of coping skills training for relapse prevention.

Furthermore, interventions of using self-help materials seem as effective as interventions based on individual or group counseling. Five trials of coping skills training in community quitters who stopped smoking for at least one week were further separated into two subgroups: trials of self-help material and trials of counseling. The pooled OR of coping skills training is 1.46 (95% CI: 1.05 to 2.05) for self-help material trials and 1.41 (95% CI 1.02 to 1.94) for counseling trials [19]. A more recently published meta-analysis also found that written self-help materials were the only type of relapse prevention intervention for unaided quitters with established efficacy [24].

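### The example mediation equations contain only arm and mediator, so the path from coping skills to relapse is open to baseline confounding and a*b may be biased in either direction (minor)

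*Protocol article*

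**What the plan says.** The mediation text is in the Data analysis plan of the protocol article. It announces the work with "We will also use more complex methods for the exploratory mediation analysis" and presents the model with "As an example, the Single-Mediator model consists of three equations". Equation (1) regresses relapse on arm, equation (2) regresses relapse on arm and mediator, and equation (3) regresses the mediator on arm. No other term appears. The estimator follows: "Then, the mediating effect of M could be quantified by a*b". The mediator is described as "M is the mediating variable (for example, time spent on reading the booklets, acquisition of coping skills, and so on". The purpose is also given: "These exploratory mediation analyses will help understand how and why the intervention works or does not work".

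The section Baseline and follow up data collection lists what is recorded at enrolment. Besides age, gender and occupation, this includes "heaviness of smoking index, smoking and quitting history, and level of confidence to remain abstinent". Under Participant recruitment and randomization, the baseline questionnaire is completed before allocation, so these variables cannot be affected by arm. Key skills are assessed in both arms at three months and tested again at 12 months.

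Nicotine dependence and number of prior quit attempts do appear in the Data analysis plan, but only as possible effect modifiers in the subgroup analyses. The article mentions neither covariate adjustment nor a no-confounding assumption for the mediation models.

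**The concern.** A randomised comparison gives unconfounded estimates of a (arm to skills) and c (arm to relapse). It gives no such protection to b. Within each arm, participants with high and low skill scores differ in whatever made them acquire skills. If one of those differences also affects staying abstinent, b picks it up, and a*b carries the bias into the estimated mechanism.

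This matters most for skill scores, which are measured in both arms and are the mechanism the trial wants to test. Two readings are at risk. In a positive trial, part of the benefit could be credited to skills that did not cause it, or a real contribution could be hidden. In a null trial, the follow-up text hopes to learn whether skills were not acquired or were acquired but did not help. The first question concerns a and is safe. The second concerns b and is exposed even when a is zero.

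**Working it through.** **The plan's own figures.** The mediation analysis has no stated figure. The abstinence rates used below come from the Sample size section and are consistent:
- Control odds 0.25/0.75 = 0.3333. Multiplied by 1.44 this is 0.48, and 0.48/1.48 = 32.4%, as stated.
- Two proportions 0.25 and 0.324, two-sided 5% (sidedness assumed), 80% power, pooled variance: [1.96 × √(2 × 0.287 × 0.713) + 0.8416 × √(0.25 × 0.75 + 0.324 × 0.676)]² / 0.074² = 586 per arm. 586/0.85 gives 690 per arm, or 1,380 in total, close to the stated 1,400.

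**Assumptions, none of them in the documents.** One baseline factor U has correlation g = 0.2 to 0.5 with skill and an odds ratio for abstinence of 1.3 to 2.0 per SD. The booklets raise skill by a = 0.3 SD. Skill itself has no effect on abstinence. The outcome is coded as abstinence; coding it as relapse flips the signs of a*b and c together and leaves the share unchanged.

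**Hand calculation.** With skill scaled to SD 1 within arm, the regression of U on skill has slope g. The unadjusted path is therefore b ≈ g × ln(OR), the spurious mediated effect is a × b, and its share of the total effect is a × b / ln(1.44), where ln(1.44) = 0.3646.

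| g | OR per SD | b | a × b | share of total |
|---|---|---|---|---|
| 0.2 | 1.3 | 0.0525 | 0.0157 | 4.3% |
| 0.3 | 1.5 | 0.1216 | 0.0365 | 10.0% |
| 0.3 | 1.6 | 0.1410 | 0.0423 | 11.6% |
| 0.5 | 2.0 | 0.3466 | 0.1040 | 28.5% |

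**Simulation of the linear equations as printed** (1,400 participants, 25% control abstinence, OR 1.44 for arm, 2,000 runs per setting), on the risk-difference scale:
- g = 0.2, OR 1.3: a*b = 0.0031 against c = 0.0732, or 4.2%.
- g = 0.3, OR 1.5: 0.0072 against 0.0736, or 9.8%.
- g = 0.5, OR 2.0: 0.0199 against 0.0699, or 28.5%.

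A separate logistic simulation (1,190 participants, g = 0.3, OR 1.6) gave b = 0.14 and a share of about 12%. If a is 0.5 SD instead of 0.3, the simulated range becomes 7% to 47%.

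**Controls.** With g = 0, mean a*b is about zero. With a = 0, mean a*b is about zero however strong the confounding. The bias in a*b therefore needs both a confounder and an effect of the booklets on skills.

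**Direction.** If g is negative, for example because more dependent quitters practise more skills, b changes sign by symmetry. The middle case becomes about −10% and would mask a true contribution.

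**After adjustment.** With U in equations (2) and (3), mean a*b lies between −0.0002 and +0.0002 in every confounded setting with a = 0.3 or 0.5. This holds because the simulation adjusts for its only confounder.

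**The case against.** The strongest reply is that no final model is fixed. The equations are an example, the effect *could* be quantified by a*b, the work is called exploratory, and covariate lists for such models usually sit in a statistical analysis plan that is not shown. The section Major limitations of the study also concedes that the interview questions may be too thin for process evaluation. Much of this stands, and it is why the severity is minor. A reader might infer that the trial has committed to an unadjusted analysis, and the text does not support that. Still, the article prints this model, names its estimator and states what it will be used to explain. Following the printed example would give a biased b whenever such a factor exists. The warning about low power and false positives belongs to the subgroup paragraph and concerns chance, not bias.

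Second, the sizes rest on assumed associations. That stands in full. Under a significance rule, the simulated rate of wrongly declaring mediation at a = 0.3 SD runs from 11% to 100%, but the article states no such test, so I do not rest the point on that rate.

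Third, the Background says that "coping skills training seems effective in secured quitters who are highly motivated to remain abstinent", and a reader might take this as evidence that motivation confounds b. It is not. The sentence says in which quitters training works, which is effect modification. Motivation is also not among the baseline variables named. That dependence or confidence drives both skill and abstinence is plausible but undocumented.

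**Conclusion.** The point holds in a limited form. The example equations leave b unadjusted, so a*b may be biased in either direction whenever the booklets change skills. Under the stated assumptions with a = 0.3 SD, inert skills would appear to carry about 4% to 29% of the total effect. These figures show what is possible; they do not estimate the bias in this trial.

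A reader might go further and infer that useless skills could appear to account for the whole benefit. Nothing supports that: even at a = 0.5 SD with the strongest confounder tried, the spurious share stays below half. Nor do the documents show that the bias must favour the booklets.

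Severity is minor. The primary and secondary outcomes and the cost-effectiveness analysis do not depend on these equations.

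**What to change.** For the skill mediators measured in both arms, add the same pre-randomisation covariates to equations (2) and (3): heaviness of smoking index, confidence to remain abstinent, quitting history, age, gender and occupation. Make the adjusted a*b the main mediation estimate. If a share of the total effect is reported, put the same covariates in equation (1) so that the parts add up.

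State that unmeasured confounding remains, and that adjustment does not deal with reverse causation when skills are assessed after a relapse. Add one simple sensitivity analysis: report how strongly a residual common cause would have to be related to skill and to abstinence to bring a*b to zero. The relation b ≈ g × ln(OR) is enough for this.

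The cost is a few lines of analysis text and code, with no new data. Naming the covariates in advance also prevents choosing them after the results are seen.

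### The mediation formula's bracketed alternative, c'-c, has the opposite sign to a*b under the plan's own equations; it should read c-c'

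*Protocol article*

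**What the plan says.** The mediation paragraph of the Data analysis plan introduces its model with "As an example, the Single-Mediator model consists of three equations". The equations are (1) `Y = i1 + cX + e1`, (2) `Y = i2 + c'X + bM + e2` and (3) `M = i3 + aX + e3`. All three are linear with additive errors. The variables are defined by "where Y is the dependent variable (smoking relapse), X is the independent variable (the intervention"), and M is a mediator such as reading time or acquired coping skills. The summary measure follows: "the mediating effect of M could be quantified by a*b (or c'-c").

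The purpose and status are stated in "These exploratory mediation analyses will help understand how and why the intervention works or does not work". No link function is named for these equations. Earlier in the same section, the statistic for arm comparisons is set by "The comparison of smoking abstinence rates (and any other binary outcomes) between the two trial arms will be carried out using OR", and logistic regression is named for the exploratory subgroup analyses.

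**The concern.** The text offers two expressions as the same quantity, but the equations printed just above make one the negative of the other. If the booklets raise coping skills (`a > 0`) and skills lower relapse (`b < 0`), then `ab` is negative, which is a mediated benefit. The bracketed form is positive and would be read as skills increasing relapse.

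The direction of the mediated effect is what this analysis is meant to supply. Under Baseline and follow up data collection, the three-month call is designed largely around process measures, so that a null result can be traced either to skills not acquired or to skills that did not help. A reversed sign would give the wrong answer to that question.

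**Working it through.** **Inputs.** The three equations and the definitions of Y, X and M come from the Data analysis plan. The Sample size section supplies "The abstinence rate of four-week quitters at 12 months is estimated to be 25.0% in the control and 32.4% in the intervention group". It derives the second rate from an odds ratio of 1.44. The documents give no values for `a`, `b` or `c'`, so those used below are assumptions.

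**Planning figures first.** Control odds are 0.25/0.75 = 0.333. Multiplied by 1.44 this is 0.480, and 0.480/1.480 = 0.324, as printed. The section continues "Assuming alpha = 0.05 and 1-beta = 0.8 and a dropout rate of 15"%. Two proportions with a pooled null variance and a two-sided test (sidedness is not stated) need 586 per arm. Then 586/0.85 = 689.4, rounded up to 690, or 1,380 in total against about 1,400. The design figure reproduces, and nothing below depends on it.

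**Step 1: the identity.** Put (3) into (2):

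`Y = i2 + c'X + b(i3 + aX + e3) + e2 = (i2 + b*i3) + (c' + ab)X + (e2 + b*e3)`

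Matching the coefficient of X with (1) gives `c = c' + ab`. Hence `ab = c - c'` and `c' - c = -ab`.

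**Step 2: can recoding rescue the printed form?**
- Reversing Y flips `b`, `c` and `c'`, so `ab` and `c - c'` flip together.
- Reversing X flips `a`, `c` and `c'`, so again both flip together.
- Reversing M flips `a` and `b`, so neither `ab` nor `c - c'` changes.

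No coding makes `c' - c` equal to `ab` unless both are zero.

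**Step 3: size at the planning rates.** Take relapse as the complement of abstinence: 75.0% control, 67.6% intervention. On the risk-difference scale `c = 0.676 - 0.750 = -0.074`. Let the mediator carry a share s of this (assumed), so `c' = -0.074(1 - s)`.

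| s | `c'` | `ab = c-c'` | printed `c'-c` |
|---|---|---|---|
| 0.25 | -0.0555 | -0.0185 | +0.0185 |
| 0.5 | -0.037 | -0.037 | +0.037 |
| 1 | 0 | -0.074 | +0.074 |

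**Step 4: does a binary Y disturb this?** Relapse was simulated as binary, with 75% control relapse, 1:1 allocation and a normal mediator with SD 1. Assumed values were `a` = 0.3 or 0.5; `b` = -0.3, -0.7, -1.0 or -1.5 log-odds per SD of M; and `c'` = 0 or -0.2 log-odds. These 16 combinations were run at N = 1,400 and at N = 1,000,000, making 32 settings. All three equations were fitted by least squares, then (1) and (2) by logistic regression. Selected results at N = 1,000,000:

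| assumed `a`, `b`, `c'` | linear `ab` | linear `c-c'` | linear `c'-c` | logistic `ab` | logistic `c-c'` | logistic ratio `(c-c')/ab` |
|---|---|---|---|---|---|---|
| 0.3, -0.3, 0 | -0.0170 | -0.0170 | +0.0170 | -0.0904 | -0.0889 | 0.984 |
| 0.5, -0.7, 0 | -0.0647 | -0.0647 | +0.0647 | -0.3506 | -0.3206 | 0.914 |
| 0.3, -1.0, -0.2 | -0.0514 | -0.0514 | +0.0514 | -0.2968 | -0.2184 | 0.736 |
| 0.3, -1.5, -0.2 | -0.0678 | -0.0678 | +0.0678 | -0.4503 | -0.2728 | 0.606 |

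In all 32 settings `c'-c` had the opposite sign to `ab`, under both types of fit. With linear fits, `ab` and `c-c'` agreed to every decimal shown. With logistic fits at N = 1,000,000 the ratio ran from 0.984 to 0.606, a gap of about 2% to 39%. At N = 1,400 sampling error widened this to 1.013 down to 0.604.

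**The case against.** The strongest reply is that the slip has little reach. The first-named measure, the product, is right. The equations are an illustration, the wording is permissive, and the analysis is labelled exploratory. A reversed report requires someone to choose the bracketed form and overlook the separately estimated coefficients, which would show the conflict. The section also plans tables and plots of abstinence against mediators, which show direction without any formula. All of this stands and limits the consequence. It does not make the formula right. Text extraction does not explain it either: the prime is legible in equation (2) and in the formula, and what is wrong is the order of subtraction.

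A reader might also infer something stronger: that because relapse is binary, the two forms must differ in size as well. The documents do not support that. The printed equations are linear, and linear fits to the same participants preserve the equality whatever the type of Y. The odds ratio is set for arm comparisons and logistic regression is named for subgroups; neither is prescribed for the mediation model. A logistic fit is a plausible reading but not a stated one, and any percentage gap then depends on mediator strengths the documents do not give. The choice of link may properly sit in a full protocol or SAP, so its absence here is not a fault.

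**Conclusion.** The bracketed formula is wrong as written. This follows from the plan's own equations and needs no assumption about mediator strength, coding or link. Under those equations the error is one of sign only, with magnitude unchanged. It matters only if the difference form is used, in which case a protective mediator is reported as harmful. The primary outcome analysis and the sample size are untouched.

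The scale issue is a conditional note, not a second error. If equations (1) and (2) are fitted as logistic models, `ab` and `c-c'` are no longer the same quantity. The 2% to 39% gap describes the assumed grid of `a`, `b` and `c'`, is small for weak mediators, and is not a prediction for this trial.

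**What to change.** Replace `c'-c` with `c-c'` in the mediation paragraph. If the outcome equations are to be fitted as logistic models, add one sentence saying so and saying that the difference of logistic coefficients will not be treated as interchangeable with the product. If they are fitted as the linear equations printed, no such sentence is needed. The cost is one corrected expression and at most one sentence, with no change to data collection, sample size or the primary analysis.
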